#### 2.6.2. Neuromuscular Stimulation (NMS)

In the NMS group, the electrical stimulation will be delivered using Wellcare Digi-Stim^®^ (Sanowell, Alzenau, Germany) with 4.0 × 4.0 cm^2^ electrodes placed on the skin. The patient will be seated during electrical stimulation. Electrical stimulation will start with the flexors and then the extensors of the arm and the hand. The same two criteria as in the rPMS group will be used to determine the stimulation intensity: a painless stimulation and a muscle contraction of at least 50% pROM. The stimulation frequency of the electrical stimulation will be 20 Hz, with an on phase of two seconds and an off phase of three seconds. Each muscle group will receive 25 muscle contractions in a 12 min session. Patients will be stimulated daily from Monday to Friday for three weeks, for a total of 15 stimulation sessions.

### 2.7. Outcome Measures

The primary outcome is the difference between the Fugl–Meyer Assessment for Upper Extremity (FMAUE_Diff_) scores before and after the three-week stimulation session, calculated as follows: FMAUE_Diff_ = (FMAUE_post_ − FMAUE_pre_)/FMAUE_pre_.

The secondary outcomes are KADL, TUG, MAS, and TaS, which are calculated in the same way as the primary outcome of FMAUE_Diff_.

Correlation analyses will be used to analyze the relationship between arm spasticity (MAS and TaS), arm function (FMAUE), and independence in ADL (KADL) in each intervention group (rPMS and NMS). For this reason, a sum score will be calculated for a total MAS score (MAS_total_) of all the muscles assessed. The change in this score (between pre and post, MAS_total-Diff_) and TaS (TaS_Diff_) is correlated with the change in FMAUE (FMAUE_Diff_) as well as with the change in KADL (KADL_Diff_).

For each patient, stimulation and testing will be performed at the same time from Monday to Friday between 09:00 and 12:00.

During the trial, included patients may not be enrolled in other trials, treated with botulinum toxin or antispastic drugs, receive peripheral electrical stimulation, or receive peripheral or central magnetic stimulation (see Figure 2).

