## Abstract

Background/Objectives: Innovative therapies are needed to reduce disability, facilitate activities of daily living, and improve the quality of life in patients with stroke. Non-invasive methods of stimulating the peripheral and central nervous system are increasingly being used to enhance the effects of existing therapies in stroke rehabilitation. One potentially relevant method for achieving greater improvement is repetitive peripheral magnetic stimulation (rPMS). This randomized controlled trial (RCT), the Peripheral MAgnetic stimulation in patients with spastic hemiparesis after Stroke Trial (REPMAST), will investigate whether rPMS improves upper extremity function, spasticity, and activities of daily living in patients with stroke compared with neuromuscular stimulation (NMS). Methods: REPMAST is an interventional, randomized controlled single-blinded study. Patients with subacute stroke are randomized to receive rPMS or NMS five days a week for three weeks in addition to standard rehabilitation therapy. The primary outcome is the change in the Fugl–Meyer Assessment for Upper Extremity between the beginning and end of the stimulation sessions. Secondary outcomes include changes in the Katz Index of Independence in Activities of Daily Living, the Timed Up and Go Test, the Modified Ashworth Scale, and the Tardieu Scale. A total sample size of 138 patients (69 in each group) is required to investigate the superiority of rPMS compared with NMS. Conclusions: The aim of this RCT is to provide evidence for an effective peripheral stimulation treatment for stroke recovery.

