### 2.3. Sample Size Calculation

REPMAST is designed to show the superiority of rPMS over NMS. Recently, the effect size of rPMS was calculated to be r = 0.68 for the FMAUE and r = 0.60 for the Wolf Motor Function Test when comparing rPMS with standard therapy [21]. A smaller effect size is expected here, as the comparison between rPMS and NMS contrasts two interventions. As there is still no RCT directly comparing rPMS and NMS, the final sample size was first compared by conducting a feasibility pilot study with 20 patients with stroke (10 in each intervention group) using the same inclusion and exclusion criteria as described above. According to the results of the feasibility pilot study, we found an effect size of 0.6 on FMAUE_Diff_ (the difference between Fugl–Meyer Assessment scores before and after the three-week stimulation session) for the rPMS group. Accordingly, to achieve a 90% statistical power to detect differences in FMAUE_Diff_ between the two groups at the 5% significance level (2-sided), a total sample size of 120 patients is required [25]. With an estimated drop-out rate of 15%, a total sample size of 138 patients (69 in each group) is required for this study.

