### 2.4. Clinical Assessment

Demographic data will be recorded at the measurement time point ‘pre’ before the intervention. Imaging data are used to determine the territory affected by the stroke. This will be followed by a medical history and a physical and neurological examination.

The following scales will be used to quantify neurological deficits, as assessed by trained raters before the intervention (‘pre’), at the end of the first week (T1), at the end of the second week (T2), and at the end (‘post’) of the three-week stimulation session: the Fugl–Meyer Assessment for Upper Extremity (FMAUE), an index to assess the sensorimotor impairment; the Katz Index of Independence in Activities of Daily Living (KADL) for the independence in activities of daily living (ADL); the Timed Up and Go Test (TUG) to measure mobility [26]; and the Modified Ashworth Scale (MAS) [27] and Tardieu Scale (TaS) [28] for spasticity.

The Fugl–Meyer Assessment for Upper Extremity (FMAUE) consists of 33 items with a maximum score of 66. Each item is scored on a 3-point scale of 0 points (unable to perform), 1 point (partially able to perform), and 2 points (fully able to perform). The FMAUE includes the following assessment categories: shoulder–elbow–forearm function, wrist function, hand function (subscore C), and coordination/speed [29]. The FMAUE generally has a very high inter-rater reliability, especially the subscale for upper extremity motor skills, which is used in this study [30,31,32]. This test also shows high sensitivity for patients with severe to moderate impairment [29].

The Katz Index of Independence in Activities of Daily Living (KADL) assesses the ability to perform ADLs independently in six functions, including bathing, dressing, toileting, transferring, continence, and feeding. Patients score ‘yes’ or ‘no’ for independence in each of the six functions. A score of 6 indicates full function, 4 indicates moderate impairment, and 2 or less indicates severe functional impairment [33]. The KADL has an excellent intra-rater reliability (intercorrelation coefficient, ICC= 1.000) and internal validity (ICC = 0.999) [34].

To measure mobility, the change in time for the Timed Up and Go Test (TUG) will be assessed [26]. The TUG measures the time taken for a patient to get up from an armchair, walk 3 meters, turn around, walk back, and sit down again [26]. This widely used and well-known test has very good inter- and intra-rater reliability (ICC = 0.99) [26].

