### 2.8. Statistical Analysis

Statistical analysis will be based on the intention to treat analysis using IBM SPSS Statistics 29 (IBM, Armonk, NY, USA). The Kolmogorov–Smirnov Test will be used to test for normal distribution. Levene’s test will be used to assess the equality of variances between groups. If there is no normal distribution, the Mann–Whitney-U test will be used; otherwise, analysis of variance (ANOVA) will be used to test for differences in the repeated measures of FMAUE (pre, T1, T2, and post). In this 2 × 2 factorial design, group will be the independent factor and time will be the dependent factor. Post hoc analyses will be performed for significant main effects and interactions. One-way ANOVA will be used to ensure that the baseline FMAUE scores before the test are not statistically significant between the two groups. The same analysis will also be performed for KADL, TUG, MAS, and TaS.

For the within-group analysis (pre- and post-test), a paired *t*-test will be used if the distribution is normal; otherwise, the Wilcoxon test will be used.

For FMAUE_Diff_, two-sample *t*-tests will be used to test for the difference between the two groups (rPMS and NMS) if the distribution is normal. If the distribution is not normal, the Wilcoxon test will be used. The same analysis will be used for KADL_Diff_, TUG_Diff_, MAS_Diff_, and TaS_Diff_.

To analyze the relationship between arm spasticity (MAS) and arm function (FMAUE) and independence in ADL (KADL) in each intervention group (rPMS and NMS), correlation analyses between the MAS_total-Diff_ and (TaS_Diff_) and FMAUE_Diff_ as well as KADL_Diff_ will be used.

For missing follow-up measurements, the Last Observation Carried Forward (LOCF) procedure will be applied by inserting the most recent present value before.

The level of statistical significance will be set at *p* < 0.05, and Bonferroni correction will be used for multiple comparisons.

The effect size will be calculated using Cohen’s *d* according to the formula mean difference between two groups divided by the result of the pooled standard deviation (the pooled standard deviation is calculated as (=√[(standard deviation rPMS^2^ + standard deviation NMS^2^)/2])). The effect size will be defined as small (0.2), medium (0.5), or large (0.8) [40].

The primary safety endpoint is the incidence of seizures and headaches during the intervention period.

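### The primary outcome is defined by formula as change divided by baseline but described as a plain difference; the scale of the 0.6 effect size is unclear, and an analysis in FMAUE points adjusted for baseline is the better choice

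*Protocol article*

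**What the plan says.** All places are in the protocol article.

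- **Abstract:** "The primary outcome is the change in the Fugl–Meyer Assessment for Upper Extremity between the beginning and end of the stimulation sessions". No division by baseline is mentioned.
- **Section 2.3 (Sample Size Calculation):** FMAUE_Diff is explained as "the difference between Fugl–Meyer Assessment scores before and after the three-week stimulation session". The pilot effect size of 0.6 is reported for this variable and leads to 120 evaluable patients for 90% power at a two-sided 5% level.
- **Section 2.7 (Outcome Measures):** the sentence opens with "The primary outcome is the difference between the Fugl–Meyer Assessment for Upper Extremity (FMAUE_Diff_) scores before and after the three-week stimulation session" and then gives the formula "FMAUE_Diff_ = (FMAUE_post_ − FMAUE_pre_)/FMAUE_pre". The secondary outcomes are computed the same way.
- **Section 2.8 (Statistical Analysis):** for FMAUE_Diff, "two-sample *t*-tests will be used to test for the difference between the two groups (rPMS and NMS) if the distribution is normal"; otherwise a Wilcoxon test is used. Separately, "analysis of variance (ANOVA) will be used to test for differences in the repeated measures of FMAUE (pre, T1, T2, and post"), with group and time as factors. Baseline is handled by a test alone: "One-way ANOVA will be used to ensure that the baseline FMAUE scores before the test are not statistically significant between the two groups".
- **Sections 2.2 and 2.4:** eligibility asks for at least one point in FMAUE subscore C and sets no lower limit on the total. The scale "consists of 33 items with a maximum score of 66".

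**The concern.** There are two linked problems.

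First, a difference in points and a fraction of baseline are different variables with different standardised effects. One name, FMAUE_Diff, is used for both, and the sample size rests on that name. A reader cannot tell which scale the 0.6 belongs to, or in what units the trial will report its main result.

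Second, if the formula is taken as written, the same gain counts for more the lower the patient starts. The ratio is right-skewed, its spread depends on baseline, and it remains negatively related to baseline, so dividing does not remove the influence of the starting score. The between-group test of FMAUE_Diff has no baseline covariate. Testing baseline for significance does not ensure balance: under randomisation any difference is due to chance, a non-significant result does not show that the groups are alike, and the plan attaches no action to the result.

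At stake are the power of the primary comparison and a clear meaning for its estimate.

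**Working it through.** **1. The plan's own figure.** Inputs from section 2.3: d = 0.6, two-sided 5%, 90% power; 1:1 allocation from section 2.5.

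- Normal approximation: n per arm = 2 × (1.960 + 1.282)² / 0.6² = 58.4, so 59 per arm, 118 in total.
- Exact two-sample t-test: 59.35, so 60 per arm, 120 in total, with power 90.3%.

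The stated 120 is reproduced. It holds for whichever variable has d = 0.6.

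**2. What the ratio does.** The value is gain / baseline.

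- A 6-point gain is 6/4 = 150% from a baseline of 4, and 6/50 = 12% from a baseline of 50.
- A 5-point gain is 125% from 4, 50% from 10, 12.5% from 40 and about 8% from 60.

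In simulations with an additive effect, the fifth of patients with the lowest baselines supplied 76–78% of the total variation in the ratio when baselines ran from 4 to 60, and 37% when they ran from 20 to 55. Equal weight would be 20%.

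**3. Power of the planned procedure.** The documents give no SD, baseline distribution or gain model, so these are assumptions: 60 per arm; change SD 8 points; group difference 0.6 × 8 = 4.8 points, the same for everyone; common gain 5 points; uniform baselines; scores rounded and held within 0–66. The planned procedure is a Kolmogorov–Smirnov check (with estimated mean and SD), then the t-test, or the Wilcoxon rank-sum test if normality is rejected.

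| Baseline range | Planned procedure on ratio | ANCOVA in points | t-test on raw change |
|---|---|---|---|
| 4–60 | about 74% | about 90% | about 90% |
| 10–55 | about 82% | about 90% | about 90% |
| 20–55 | about 85% | about 90% | about 90% |

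Repeat runs of the planned procedure gave 73–75%, 79–82% and 84–85%, with 89–90% in points. Normality was rejected in nearly all runs for 4–60 and about 90% for 10–55, so the rank test does most of the work there. With no treatment effect, all methods rejected in about 5% of runs.

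**4. What ANCOVA adds to raw change.** In step 3 the post score rises one for one with baseline, so ANCOVA and raw change perform alike; the gain comes from dropping the division. If pre and post variances are equal with correlation ρ, the ANCOVA variance is (1 + ρ)/2 times that of raw change. If 0.6 refers to raw change, the required total of 120 becomes 90 (ρ = 0.5), 102 (ρ = 0.7) or 114 (ρ = 0.9); with 120 patients, power is about 97%, 95% or 92%.

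**5. When the ratio does well.** If gain, effect and error SD all scale with baseline, the t-test on the ratio reached 85–90% against 78–89% for ANCOVA. If gain and effect scale but the error SD does not, ANCOVA was ahead again: 76–90% against 31–86%.

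**The case against.** - **The plan has a rank-test fallback.** This stands. Quoting power for the t-test on the ratio alone (51–54% for baselines 4–60) would describe a test that section 2.8 would rarely use in that setting. Ranks also limit the pull of extreme ratios, so the result cannot be said to rest on a few severely impaired patients. The fallback recovers part of the loss, not all of it, and the table already includes it.
- **The 0.6 may already be on the ratio.** A reader might infer that the ratio does not have the planned effect and that the trial is underpowered. The documents do not support that. Section 2.3 attaches 0.6 to FMAUE_Diff, the variable that section 2.7 defines by formula. If the pilot used the formula, 60 per arm gives 90% t-test power by construction. If it used points, the loss above applies.
- **The size rests on outside inputs.** This stands. Low baselines are permitted, but nothing shows that they will be common, and with baselines of 20–55 the loss is only about 5 percentage points.
- **FMAUE in points is also analysed, by repeated-measures ANOVA.** True, and that analysis contains the pre value. It does not use baseline as a covariate, and it does not change how FMAUE_Diff is defined or tested.

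**Conclusion.** The contradiction is certain: the formula is a relative change, and the wording in three places is a plain change or difference. The scale of the 0.6, and so the basis of the 90% power, cannot be settled from the document.

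Dividing by baseline is a weak choice on a 0–66 scale with no floor on entry. Under an additive effect of 0.6 SD in points, the planned procedure loses roughly 5 to 16 percentage points of power (85% to 74%, against about 90%), depending on how low baselines reach. These figures are conditional on the assumptions listed. The direction reverses only if gain, effect and error SD all grow in proportion to baseline, which is hard to sustain on a scale capped at 66.

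A reader might take the skewed ratio or the lack of adjustment to mean that false positives are inflated. They are not: type I error stayed near 5% throughout. The matter is one of power and interpretability, and it should be put right while the data are still blinded.

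**What to change.** Before unblinding:

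1. Define the primary outcome as FMAUE at post, in points, analysed by ANCOVA with group and FMAUE at pre as covariate. Report the adjusted group difference with a 95% confidence interval.
2. Remove the baseline significance test, since the adjustment is made whatever the baseline difference.
3. Keep percentage change as a descriptive summary only. Review the same formula for the secondary outcomes, where it is undefined at a baseline of zero (possible for the Katz index and for the Tardieu R2 − R1 angle).
4. Use one definition in the Abstract, section 2.3 and section 2.7.
5. State whether the pilot 0.6 was measured in points or on the ratio. If in points, 120 evaluable patients remain sufficient. If on the ratio, recompute the effect in points from the pilot data and recheck the sample size.

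Cost: the primary outcome definition of a registered, ongoing trial has to be amended and the change documented. No new patients, visits or measurements are needed. Some power is given up if gain, effect and error SD all scale with baseline.

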Spasticity is assessed using the Modified Ashworth Scale (MAS) [27]. The MAS is a semi-quantitative measure ranging from 0 to 4 points that is used to assess the severity of spasticity. MAS scores for the shoulder, upper arm flexor wrist, and finger flexors/extensors will be evaluated for each patient. The psychometric criteria of the MAS are described very controversially in the literature, ranging from unsatisfactory to very good [35,36]. For this reason, the Tardieu scale will also be used to assess spasticity.

The Tardieu Scale (TaS) quantifies spasticity by assessing the response of the muscle to different stretch velocities and by determining the spasticity angle. A goniometer is used to measure R2 and R1. The patient is seated during the test. The stretch velocity of V1 and V3 is used to measure R2 and R1, respectively. The quality of the muscle response is also assessed using the stretch velocity of V3. The difference between R2 and R1 is used as a measure of the dynamic component of spasticity [28]. The test–retest reliability of the Tardieu scale is reported to be moderate to very good [37], with good inter-rater and very good intra-rater reliability [38].

All assessments will be recorded by therapists who are not involved in the study. Before the study starts, standardized training will be given to all those responsible for collecting the assessments. Side effects will also be recorded and compared between groups.

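### The baseline-ratio formula set for the secondary outcomes has no value when KADL or the Tardieu difference (or a single-muscle MAS) is 0 at baseline

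*Protocol article*

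**What the plan says.** Section 2.7 gives the primary change score as "FMAUE_Diff_ = (FMAUE_post_ − FMAUE_pre_)/FMAUE_pre", and extends it to the others: "The secondary outcomes are KADL, TUG, MAS, and TaS, which are calculated in the same way as the primary outcome of FMAUE_Diff". The same section correlates the changes in MAS_total and TaS with the changes in FMAUE and KADL.

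Section 2.8 commits to intention to treat. It compares FMAUE_Diff between groups with a two-sample t-test, or a Wilcoxon test if the distribution is not normal, and adds: "The same analysis will be used for KADL_Diff_, TUG_Diff_, MAS_Diff_, and TaS_Diff". Its only missing-data rule carries the last value forward when a follow-up measurement is absent.

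Section 2.4 describes the scales:
- KADL: "Patients score ‘yes’ or ‘no’ for independence in each of the six functions", with the lowest band given as "2 or less indicates severe functional impairment".
- MAS: "The MAS is a semi-quantitative measure ranging from 0 to 4 points", and "MAS scores for the shoulder, upper arm flexor wrist, and finger flexors/extensors will be evaluated for each patient".
- TaS: "The difference between R2 and R1 is used as a measure of the dynamic component of spasticity".

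Section 2.2 sets two relevant entry floors: at least one point on subscore C of the FMAUE, and a MAS of at least 1 with no muscle named. It sets none for KADL or TaS.

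**The concern.** A relative change needs a baseline that cannot be 0. The formula was written for FMAUE, where the entry criteria ensure this. It was then carried over to scales where 0 is an ordinary baseline value.

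Two things are at stake. First, a randomised patient with complete measurements may have no value on a prespecified secondary outcome. For KADL these would be the most dependent patients; for TaS, those without a measurable dynamic component. Leaving them out conflicts with the stated intention-to-treat analysis. With no rule in place, the choice to exclude them, add a constant or switch to raw change would be made after the data are in. Second, where the ratio exists, it gives the same one-point change very different weight depending on the baseline.

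**Working it through.** **The plan's own figure.** The only sample size stated is for FMAUE_Diff (section 2.3). With an effect size of 0.6, 90% power and two-sided 5%, the t-based calculation gives 59.35, so 60 per group and 120 in total, as stated. Then 120 × 1.15 = 138, also as stated. No sample size, power or share of zero baselines is given for a secondary outcome, so 138 serves below only as a denominator.

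**Can the denominator be 0?** Inputs are the scale descriptions in section 2.4 and the entry criteria in section 2.2.

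| Quantity | Lowest possible baseline | Ratio always defined? |
|---|---|---|
| FMAUE | 1 (subscore C is at least 1) | Yes |
| KADL | 0 (six yes/no items, no floor) | No |
| TaS, R2 − R1 | 0 (angles coincide, no floor) | No |
| MAS_total | 1, if any assessed muscle meets the entry criterion | Yes |
| MAS, single muscle | 0 (criterion may be met in another muscle) | No |
| TUG | above 0 (a time) | Yes, if the test is performed |

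Section 2.8 tests a MAS_Diff, but neither section says whether it is per muscle or a total. The single-muscle row therefore applies only if it is per muscle.

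**What the formula returns at 0.** For KADL with pre = 0:
- post = 0: (0 − 0)/0 = 0/0, no value.
- post = 2: (2 − 0)/0 = 2/0, no value, although the patient gained two functions.

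TaS fails in the same way when R2 − R1 = 0 at baseline. The Wilcoxon alternative does not settle it: a positive x/0 could be placed at the top of the ranking, but the plan does not say so, and 0/0 has no rank. Carrying the last value forward replaces a missing post value and leaves the zero denominator in place.

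**Weight of one point where the ratio exists.** For a one-point KADL gain the ratio is 1/pre:

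| pre | 1 | 2 | 3 | 4 | 5 |
|---|---|---|---|---|---|
| change | +100% | +50% | +33% | +25% | +20% |

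The spread is 1.00/0.20 = 5-fold. For MAS, 2 to 1 is (1 − 2)/2 = −50%, while 1 to 2 is (2 − 1)/1 = +100%.

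**How many patients.** The documents do not say. With assumed shares f of zero baselines on one outcome, 138 × f gives:

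| f | 2% | 5% | 10% | 20% | 30% |
|---|---|---|---|---|---|
| patients without a value | 2.8, about 3 | 6.9, about 7 | 13.8, about 14 | 27.6, about 28 | 41.4, about 41 |

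**The case against.** The best defence is that the damage is contained, and most of it stands.

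- Section 2.8 also plans a repeated-measures comparison of FMAUE over the four visits and extends it to KADL, TUG, MAS and TaS, along with within-group pre/post tests. As written, these use the scores themselves, where 0 is an ordinary value. A reader might infer that the spasticity and daily-living questions will be answered only in a selected subset. The documents do not support that: only the _Diff comparisons and some correlations are affected.
- A reader might infer that intention to treat fails for every secondary outcome. It does not. MAS_total stays at 1 or more if any assessed muscle meets the entry criterion, and a TUG time cannot be 0. A patient unable to perform TUG at baseline has a missing value, which raw change would not cure either.
- In the correlations, FMAUE_Diff and MAS_total-Diff are defined. Only KADL_Diff and TaS_Diff can be undefined.
- A KADL of 0 means dependence in all six functions, which may be uncommon. No share can be defended from the documents.
- The unequal weighting is a general objection to percentage change, separate from the undefined values.

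What the defence does not remove is that the between-group tests on KADL_Diff and TaS_Diff are prespecified in their own right, and their definition fails at an attainable baseline. This is not detail left to an analysis plan, because the article states the formula and extends it expressly.

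**Conclusion.** The point holds in limited form. As written, KADL_Diff and TaS_Diff have no value for a randomised patient whose baseline is 0, and the same is true of MAS_Diff if it is computed per muscle. This conflicts with the stated intention-to-treat analysis, and the missing-data rule does not reach it. Where the KADL ratio exists, it weights a one-point gain up to five-fold differently.

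The number of patients affected is unknown; the 2% to 30% range above is assumption. That zero baselines will occur is plausible in rehabilitation inpatients but is not shown in the documents. The conclusion about MAS_total assumes that the muscle meeting the entry criterion is among those assessed. The primary outcome and its sample size are not affected by the zero denominator. Severity: should be fixed, secondary outcomes only.

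**What to change.** In sections 2.7 and 2.8:

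1. Replace the sentence that extends the primary formula. Define KADL_Diff, MAS_Diff and TaS_Diff as absolute change, post − pre. Alternatively, analyse the post score adjusted for the pre score, with a rank-based or ordinal model for KADL.
2. State whether MAS_Diff is per muscle or the total, and that the TaS quantity analysed is R2 − R1, if that is what is meant.
3. Use the absolute changes in KADL, TaS and MAS_total in the correlation analyses.

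Either option gives a value to every patient with measured pre and post scores. Absolute change also counts each KADL point equally. The cost is protocol wording, settled before the data are analysed; no extra data or patients are needed.
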